### 18.b Fidelity of interventions

A previously-described scale has been developed by the principal investigator (PC) to evaluate adherence to 12 core treatment components of the Preventure program (e.g., goal setting, identifying and challenging automatic thoughts). The Cognitive Therapy Scale-Revised [68] and the Motivational Interviewing Treatment Integrity 3.0^49 will also be used to assess the quality of the therapy-specific skills demonstrated. Trainees will be given feedback on their performance based on these scales and each facilitator will be supported in attaining a sufficient level of program adherence and quality of delivery before running personality-targeted interventions with trial participants. The clinical research team using the three scales will evaluate a random 30% of all intervention sessions and each facilitator will be observed running at least one intervention session. In addition, an independent rater (MINT network trainer) will evaluate 10% of all intervention sessions. The evaluation data will be used to evaluate and validate the fidelity and quality of the interventions delivered.

Means fidelity/quality of supervision for each scale

| Measure                                               | Clinical Team |
|-------------------------------------------------------|---------------|
| Fidelity Checklist (0 to 6)               | 3,2           |
| Motivational Interviewing Scale (1 to 5)  | 3,24          |
| Cognitive Behavioral Scale (1 to 6)       | 3,14          |

Means fidelity/quality of intervention for each scale

| Measure                                               | Clinical Team | Independent rater |
|-------------------------------------------------------|---------------|-------------------|
| Fidelity Checklist (0 to 6)               | 3,8           | -                 |
| Motivational Interviewing Scale (1 to 5)  | 3,3           | 3,7               |
| Cognitive Therapy Scale (1 to 6)          | 3,6           | 2,9               |

 A score of 3 is classified as "satisfactory" a score of 4 is classified as "good" to fidelity

 An average of 3.5 is beginning proficiency and average of 4 is competency

 A score between 3 and 4 is classified as "competent" to adherence

**18.c Description of protocol deviation for the trial**

In the end, some schools did require active parental consent for youth to participate in this trial; therefore, not all HR youth were recruited and were provided with interventions in the intervention condition. However, these schools will remain in the study, and considered “compliant”. Only schools that agreed and were able to facilitate follow-up every year were included in the study, regardless of follow-up rate (therefore, compliant). Schools that did not agree to continue to facilitate follow-up of students were considered dropout (non-compliant) and will not be included in **the intent to treat analysis**.

Protocol deviation are defined as departure from the procedures outlined in the protocol. We used a modified intention to treat (mITT) design including only schools that were randomized and followed during 5 years. At the individual level, mITT will be all high-risk students in the schools who consented to a trial and eligible to receive intervention (Regardless of whether or not they received it). Per-protocol analysis at the individual level will exclude the students who did not receive both intervention sessions.

**18.d Description of which protocol deviation will be summarized**

Protocol deviation (PD) will be classified prior to unblinding of intervention groups.

1. During the recruitment phase, five schools were recruited and drop out after the randomisation. Among those, three schools never launched screening and baseline survey, and so were not included. One school drop out after screening and one school did deliver intervention, but failed to comply with follow-up procedures, so was also dropped from the trial and not included in mITT.
2. There were some deviations related to the data collection and the questionnaire administration. In the DEP-ADO, a missing item (“last 30 days alcohol use”) was not assessed. Therefore, the positive screen was adjusted to “greater or equal to 18” (Red). Truancy is self-reported. The CMS had to be modified to increase ceiling effects (one additional item was added in year 3, 4 and 5). Finally, the academic records were not obtained.
3. Visit completed outside of the planned window since there were two waves of recruitment, students were recruited in the 7th grade in 2012 and 2013.
4. There were also some procedures not performed. We changed intervention adherence criterion. Overall 88% of HR students received intervention, but some schools had poor implementation, so we will control for adherence, rather than require a certain level of implementation). One school closed and half the students could not be followed individually, but school remains in the study, because they provided access to student information so that they could be followed individually. One school missed a follow-up survey in year 4 and instead completed two surveys 7 months apart in the final year: they are considered compliant and in the ITT.

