#### *2.8 What are the proposed primary and secondary outcome measures?*

The **primary outcomes** of this study are self-report alcohol and illicit drug use measures in high-risk youth, including onset of drinking, binge drinking and illicit drug use, within the first two years of the follow-up, and longer-term reductions in substance use disorders in later years, assessed according to a score greater than 20 on the 'Detection of alcohol and drug problems in adolescents' questionnaire (DEP-ADO [97]). This tool has demonstrated good construct validity, internal consistency, test-retest and intermodal execution reliability in Quebec youth. Self-report measures have been found to have excellent discriminant [98] and predictive [99] validity with regards to adolescent substance-related behaviours and problems [25-27, 69] This questionnaire captures quantity, frequency of drinking, binge drinking and illicit drug use, as well as symptoms of substance abuse and dependence, reliably identifying youth with alcohol use disorders [100]. Youth who screen positive on this task will be contacted outside of the school setting to participate in a confidential phone or face-to-face interview, in which DEP-ADO will be administered by a clinician to confirm substance use disorder diagnosis.

**Intermediate secondary outcomes** are cognitive functioning. Global cognitive functioning, executive function and reward sensitivity will be assessed using neuropsychological measures relating to each of the hypotheses outlined in section 1.2. All cognitive tasks will be administered annually, during a 50-minute class period using computerised neuropsychological batteries developed, validated and shown to predict future academic and work performance by PI [name] et al. [100] and physical aggression by PI [name] et al. [71].

1. Global Effects Hypothesis will be tested using a computerised progressive matrices task [101] and a general knowledge task based on that used in [71], as proxies for global cognitive functioning. A pattern recognition task, a spatial recall task, verbal recall task and a visual reproduction recall task will be used to measure immediate and delayed visual and verbal memory, following [name] et al. [100]. Similar cognitive scales have identified youth with alcohol use disorders [37].

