**19. Definition of Analysis populations e.g. modified ITT (mITT)**

The **mITT** population is defined as all the schools (excluding schools dropped out after randomization, c.f. Figure 1, whose participation rate was too low along with administration difficulties).

The units of analysis are at both the student's level and school's level for all outcomes.

Schools included in mITT:

1. Completed baseline survey
2. Agreed to continue with study protocol and remain in study post baseline (Delivered 50% of follow-up surveys sessions 2/4)

Child included in mITT:

1. Assented and parent passive or active consent
2. Completed baseline survey
3. Provided reliable substance use (Dep-Ado, all 36 items used to identify SUD) and SURPS (All 23 items) data at baseline and year 5.
4. High Risk status participants (n=709) will be included.

Per-protocol will exclude participants that did not attend the two sessions of intervention.

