## APPENDIX

### Appendix 1: Timing of outcome assessments

| Primary Outcome                                                                                         |                    |
|----------------------------------------------------------------------------------------------------------------|--------------------|
| Measure                                                                                                 | Time Frame  |
| DEP-ADO: Self-reported alcohol and drug problems ( $\geq 18$ )                                                 | At follow-up 4     |
| Secondary Intermediate Outcomes                                                                         |                    |
| Measure                                                                                                 | Time Frame  |
| Global cognitive function:                                                                                     |                    |
| Adaptation of the Cultures Figure Task (CFT)                                                      | At each time point |
| Adaptation of the 'Dot Location' test, a subtest of the Child Memory Scales (CMS)                 | At each time point |
| Executive function:                                                                                            |                    |
| Adaptation of the Go/No-Go Passive Avoidance Learning Paradigm (PALP)                          | At each time point |
| 'Find the phone' is a task based on the Self-Order Pointing Task                                  | At each time point |
| Other secondary outcomes                                                                                |                    |
| Measure                                                                                                 | Time Frame  |
| DEP-ADO  age of drinking and substance use onset, binge drinking items                            | At each time point |
| SDQ  : Conduct problems, peer problems, emotional problems and hyperactivity/inattentive symptoms | At each time point |
| Depression and anxiety symptom severity (BSI)                                                                  | At each time point |

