**Appendix 3: Additional information on Outcome measures.**

Table 3: Summary of outcomes, measures and time of assessment.

| Outcomes         | Variable                                                  | Measure (items)                                                                                           | Grade at time of assessment |
|------------------|-----------------------------------------------------------|-----------------------------------------------------------------------------------------------------------|-----------------------------|
| Primary   | Substance abuse/dependence                                | DEP-ADO total score $\geq 18$ (DEPAPO_ECHELLE_TOTAL)                                                      | 8, 9, 10, 11                |
|                  | Global cognitive function                                 | Global cognitive function:                                                                                |                             |
|                  | • Non-verbal functioning and abstract reasoning           | • Adaptation of the CFT (IQ)                                                                              | 8, 9, 10, 11                |
|                  | • Verbal and visual memory (immediate and delayed recall) | • Adaptation of the CMS (DLR)                                                                             | 8, 9, 10, 11                |
|                  | Executive functioning                                     | Executive function:                                                                                       |                             |
| Secondary | • Cognitive control and response inhibition               | • Adaptation of the PALP (INH)                                                                            | 8, 9, 10, 11                |
|                  | • Spatial working memory                                  | • 'Find the phone' task (WM)                                                                              | 8, 9, 10, 11                |
|                  | Substance use onset and binge                             | • Substance use onset (DEPAPO_ALC_OC2, DEPAPO_DRUG_OC1)
• Binge items (DEPAPO_ALC_OC5, DEPAPO_ALC_OC8) | 8, 9, 10, 11                |

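### The primary case rule moved from a DEP-ADO score above 20 to 18 or more because one item was not asked, with no derivation of 18 and no check that the conclusion survives the choice

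*Combined protocol and SAP*

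**What the plan says.** Protocol 2.8 defines the later primary outcome as substance use disorder "assessed according to a score greater than 20 on the" DEP-ADO, with 20 as the figure to exceed. Students who screen positive are then to have an interview "in which DEP-ADO will be administered by a clinician to confirm substance use disorder diagnosis".

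SAP 18.d, item 2, says that the item on alcohol use in the last 30 days was not asked: "Therefore, the positive screen was adjusted to" a score "greater or equal to 18". SAP Appendix 1 lists the primary outcome as "DEP-ADO: Self-reported alcohol and drug problems" at 18 or more, at follow-up 4. Table 3 in SAP Appendix 3 uses the same threshold.

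Other passages that bear on this:

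- SAP 19 admits a student to the mITT population only with reliable DEP-ADO data, described as "all 36 items used to identify SUD". It does not say how that count relates to the item that was not asked.
- The SAP revision table has a row for version 1.1 that is blank apart from the version numbers.
- The three analyses in SAP 26.c (planned sensitivity analyses) concern imputation, per-protocol status and the interaction with high-risk status. None varies the cut-off.
- The deviation description that follows Table 3 repeats most of the 18.d list but leaves out the missing item and the new threshold. The model code printed after it uses an outcome called Flagged, which the text does not define.

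**The concern.** SAP 16 relies on a single primary endpoint and makes no multiplicity adjustment. The rule that decides who is a case on that endpoint was changed after the instrument was found to be incomplete. The SAP gives no score range for the missing item, no derivation or calibration of 18, and no date for the choice; 18.d says only that deviations will be classified before unblinding.

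A fixed allowance cannot reproduce a rule that depended on each student's own answer. The missing item measures recent drinking, a behaviour that the intervention targets, so giving everyone the same 3 points removes whatever difference between arms that item would have carried. A reader cannot tell whether the primary conclusion depends on the choice of 18, and a reader of the closing deviation list alone would not learn that the threshold changed.

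**Working it through.** **1. The planning figure, as a base.** SAP 10 gives a control rate of 10%, an intervention rate of 5%, k = 0.035/0.10 = 0.35, 50 high-risk students per school, 80% power and a false positive rate of 2.5%. I read the last as one-sided, which has the same critical value as the two-sided 5% in SAP 15. With p0 = 0.10 and p1 = 0.05:

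c = 1 + (1.960 + 0.842)² × [p0(1−p0)/50 + p1(1−p1)/50 + k²(p0² + p1²)] / (p0 − p1)²

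= 1 + 7.849 × [0.0018 + 0.00095 + 0.00153] / 0.0025 = 14.44

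This rounds up to the stated 15 schools per arm. Power at 15 is 81.6%. The planned OR is (0.05/0.95)/(0.10/0.90) = 0.474.

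**2. When the two score rules agree.** Let S be the whole-point score on the asked items and x the score that the missing item would have had. The protocol score rule is S + x ≥ 21. The SAP rule is S ≥ 18, which is the same as S + 3 ≥ 21.

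| S | SAP rule | Protocol score rule | Disagreement |
|---|---|---|---|
| 21 or more | case | case | none |
| 18 to 20 | case | case only if x ≥ 21 − S | (18; x = 0, 1, 2), (19; x = 0, 1), (20; x = 0) |
| 17 or less | not a case | case only if x ≥ 21 − S | needs x ≥ 4, for example 17 + 4 = 21 |

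The second row contains extra cases whatever the item is worth. The third row loses cases only if the item can score 4 or more. A student with 18 + 3 is a case under both rules.

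**3. What misclassification does to the odds ratio.** The documents give no share scoring 18 to 20, so every rate here is an assumption.

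*Extra cases equally common in both arms and unresponsive to the intervention.* Adding f to each arm, OR = [(0.05+f)/(0.95−f)] / [(0.10+f)/(0.90−f)] and RR = (0.05+f)/(0.10+f):

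| f | OR | RR |
|---|---|---|
| 0 | 0.47 | 0.50 |
| 0.01 | 0.52 | 0.55 |
| 0.02 | 0.55 | 0.58 |
| 0.03 | 0.58 | 0.62 |
| 0.05 | 0.63 | 0.67 |

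Expressed as specificity, with k held at 0.35: 0.99 gives 10.9% v 5.95%, OR 0.517 and power 75%; 0.98 gives OR 0.554 and power 68%; 0.95 gives OR 0.637 and power 51% (65% if the between-school SD does not grow).

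*Extra cases halved by the intervention like the rest.* 12% v 6% gives OR 0.468 and power 86%. 15% v 7.5% gives OR 0.459 and power 90%. There is no dilution.

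*Cases lost, none added.* At sensitivity 0.8 the rates are 8% v 4%, with OR 0.479 and power 75%. Power falls, but the OR hardly moves.

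**4. Whether two cut-offs bracket the protocol-rule odds ratio.** Suppose that the item scores at most 3, so that the case sets nest. Take control v intervention rates of 5% v 2.5% for above 20 on the asked items (OR 0.49), 8% v 5% for the protocol score rule (OR 0.61), and 10% v 5% for 18 or more (OR 0.47). The outer two analyses agree, yet the middle OR lies outside both. Prevalence is bracketed; the odds ratio is not.

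**The case against.** The best defence is that some lowering was needed. Dropping an item lowers the total of anyone who would have scored on it, so keeping a threshold above 20 on the shortened score would miss students who needed those points. With an item maximum of 3, six score combinations would be missed. The change is also stated openly in 18.d with its reason and is carried consistently into Appendices 1 and 3. All of that stands. It explains why a lower threshold is reasonable, but not why it should be 18.

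The continuous DEP-ADO comparison in SAP 26.b uses no cut-off. It does use the same incomplete score and addresses a mean difference, so it cannot show whether the binary result depends on the threshold.

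A reader might go further than the documents allow in four ways:

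- *The change pulls the effect toward the null.* This needs extra cases that are equally common in both arms and do not respond to the intervention. Students scoring 18 to 20 report the behaviour that the programme targets and may benefit as much as the others.
- *Every error is a false positive.* This holds only if the item is worth at most 3 points, which the documents do not say.
- *A threshold above 20 on the asked items is the protocol cut-off.* It is the stricter bound that results from setting the missing item to its minimum of 0. The protocol score rule cannot be applied to an item that nobody was asked, and Protocol 2.8 also includes clinician confirmation.
- *The count of 36 items is wrong.* The documents do not give the length of the full instrument, so 36 may already exclude the missing item.

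**Conclusion.** The concern holds as a problem of an uncalibrated and untested threshold on the single primary endpoint. The case rule changed, and 18 or more can count students whom the protocol score rule would not count; that much follows from the definitions for any weight of the item, assuming whole-point scores. How many students are affected is unknown, as are the direction and size of any effect on the odds ratio. The illustrative range runs from no dilution (OR 0.46 to 0.47, extra cases benefiting equally) to an OR of 0.52 to 0.63 (1 to 5 added percentage points per arm of unresponsive cases). The documents support neither end over the other. As the plan stands, the result is an effect on a modified screen of 18 or more; carrying it over to the protocol endpoint has not been justified.

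**What to change.** - **Add a sensitivity analysis to SAP 26.c**, labelled as added after the item was found to be missing. Re-run the model reported as primary twice: once with the missing item at its minimum for everyone (above 20 on the asked items, if that minimum is 0), and once at its maximum (above 20 minus that maximum, which equals 18 or more if the maximum is 3).
- **Present the two runs as bounds on who is a case**, not as bounds on the odds ratio. Describe the main result as an effect on the modified screen and say whether it is robust to the stricter cut-off.
- **State the missing item's score range**, and how and when 18 was chosen.
- **Reconcile the item count in SAP 19** with the item that was not asked.
- **Restore the missing item and the changed threshold** to the deviation description after Table 3, and say which cut-off defines the variable Flagged in the model code.

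The cost is at most two re-runs of an existing model with a recoded outcome (one if the item's maximum is 3), plus SAP wording. The downside is fewer events at the stricter cut-off, and so a wider interval for that analysis.

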## **2. The Proposed Trial**

### *2.1 What is the proposed trial design? E.g. Open-label, double or single blinded, etc.*

The study will use a cluster-randomised controlled design to test the effects of personality-targeted interventions on substance use and cognitive outcomes. Thirty-two schools (cluster) will agree to conduct annual surveys for 5 years with all consenting adolescents who are enrolled in Grade 7 in September 2012. Schools will be randomly assigned to 1) be trained to deliver the intervention programme and assisted in delivering the selective programme to this Grade 7 cohort or 2) assigned to receive training at the end of the trial, so that their corresponding Grade 7 cohort is never exposed to the intervention. Intervention schools will be assisted by research staff in organisation, delivery and evaluation of interventions delivered to their high risk students meeting criteria for personality risk. All schools will be assisted by our research team in arranging and implementing baseline and follow-up assessments at 12, 24, 36 and 48 months post-randomisation (Appendix B-Consort Figure).

This selective intervention involves screening all students in the first term of their Grade 7 year on personality dimensions linked to risk for substance misuse. Those scoring one standard deviation above the school mean on one of the following four dimensions will be invited to participate in coping skills workshops: Anxiety sensitivity, Hopelessness, Impulsivity, Sensation seeking. Due to the confidential nature of the selection criteria, this information will only be revealed to the teachers who deliver the training workshops. Feedback will not be provided to high risk youth or their parents.

This trial does not include a placebo condition, nor do we attempt to control for therapist contact in the control condition to avoid possible iatrogenic effects of an untested placebo intervention, which have been observed with youth interventions [90]. Furthermore, several systematic reviews of school-based interventions do not show natural reductions in youth substance use resulting from inactive group sessions.

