**18. Compliance/or adherence and protocols deviations****18.a How adherence to the intervention will be presented**

Compliance will be defined as being able to conduct all five assessments and, for intervention schools, being able to provide interventions to 85% of all high-risk youth in their school. Based on previous studies, schools generally had little difficulty complying and implementing the protocol, with only one school dropping out of the Adventure Trial due to systematic problems within the school and an impending school closure. Another intervention school was unable to complete the protocol for running sufficient interventions sessions with HR students and was thus not included in the trial. However, the main objective of the Adventure Trial was to evaluate effectiveness of the Programme, so research staff in this previous study could not offer additional support to schools if they could not deliver a certain aspect of the intervention protocol. Effectiveness will not be evaluated in the proposed study, and the current protocol will allow research staff to assist schools in meeting demands of the research or intervention protocol, thus further improving compliance rates in the proposed trial. Based on recruitment rates from the three previous trials, student participation rates are anticipated as being >85%, and with a passive parental consent procedure, we should see very little attrition due to non-consent. One of the main sources of attrition in school-based research is requiring that parents provide active, signed consent for their child to participate. Passive consent was used at various stages in the three previous trials conducted by the PI and are easily justified to an ethics committee by our data suggesting that high risk youth are more likely to volunteer to participate in these preventative interventions, but less likely to be able to provide signed consent forms from their parents, likely due to personality and related cognitive difficulties in the child or the family.

The following table provides an estimate of degree of compliance. As does school-level follow-up rate at each year (see CONSORT Figure 2).

Table 2: Participation of high-risk youth in intervention sessions and format of intervention delivery by school.

| Intervention school | Intervention Delivery      | High risk students | Students completed at least one intervention session | Students completed both intervention sessions |

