### **26.c Planned sensitivity analyses**

Sensitivity analyses will be implemented to examine plausibility of putative mechanisms underlying the effectiveness of the intervention as well as the interaction between intervention and participants' characteristics.

Sensitivity 1: Replace missing data for the binary primary outcome using multiple imputation (section 27.a).

Modification to protocol: The senior investigator never intended to report primary outcomes without replacing missing data. This was an oversight at the time of finalising the first analysis plan. We therefore have agreed to report primary outcomes after having replaced missing data using a full information method with 20 imputations (see 27.a). Therefore, this procedure will be followed for the primary and secondary analyses, and not only for Sensitivity analysis 1.

Sensitivity 2: Test effect in HR students who indeed received the intervention rather than mITT (ie Per Protocol analysis)

Sensitivity 3: Interaction between HR status and Intervention effect – does the intervention effect reveal itself at a population level?

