5. Some procedures not performed. We changed intervention adherence criteria: Overall 86% of HR students received intervention, but some schools had poor implementation which fell below our initial criteria for evaluation. We will control for adherence, rather than require a certain level of implementation. One school closed, but the school remained in the study, because they provided access to student information so that they could be followed individually. One school missed a follow-up survey in year 4 (due to natural disaster, flood) and instead completed two surveys 7 months apart in the final year: they are considered compliant and in the ITT.
6. **Deviation from planned statistical analyses:** when analysing this dataset, it became apparent that the Proc GLIMMIX method in SAS that is described in the analysis plan was not the most appropriate method to analyse this dataset, as this method required that an imputed dataset be generated in order to include all available data in the analysis. Due to the complex structure of this dataset, and the fact that data were missing at the individual and school level, multiple imputation as a method to manage missing data failed to converge, due to the fact that these models have difficulty managing high-dimensional models with correlated parameters. They either take very long to converge, or don't converge at all, especially for dichotomous outcomes. Very recently, the benefits of the Bayesian framework for managing multi-level data with missingness have been highlighted as potential solutions for social and health sciences. A number of solutions now exist using the STAN package in R. The MLM in Bayesian framework is especially useful when dealing with repeated measurements (e.g., when measurements are nested within participants) or when handling complex dependency structures in the data such as unequal sample sizes

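### The SAP says adherence will be controlled for but defines no variable, coding or model and lists no such covariate; the statement should go, and the per-protocol analysis needs a rule for controls and a non-randomised label

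*Combined protocol and SAP*

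**What the plan says.** SAP 18.a sets a school-level delivery standard for intervention schools: "being able to provide interventions to 85% of all high-risk youth in their school". Section 18.d, item 4, reports that this criterion was changed. It gives a figure, "Overall 88% of HR students received intervention", notes poor implementation in some schools, and concludes "so we will control for adherence, rather than require a certain level of implementation". Item 5 of the closing section on protocol deviations (after Appendix 3) repeats the decision, "We will control for adherence, rather than require a certain level of implementation", with a different figure: "Overall 86% of HR students received intervention".

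The sections that specify models do not mention adherence:

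- Section 26.a defines a two-level model of the arm effect at 48 months.
- Section 26.b (adjustments) lists school language, the three gender categories and, as a later change, immigration status.
- The primary model code printed at the end of the SAP has fixed terms DEM_01, Exp_Group, Language, time and time by group. None is named for adherence or attendance.
- Section 18.c keeps high-risk students in the mITT set whether or not they received the sessions.

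On the per-protocol set, section 19 says: "Per-protocol will exclude participants that did not attend the two sessions of intervention". Section 26.c lists this as Sensitivity 2: "Test effect in HR students who indeed received the intervention rather than mITT". Neither says how controls are handled. Protocol 2.1 describes the control schools as set up "so that their corresponding Grade 7 cohort is never exposed to the intervention".

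**The concern.** Attendance is observed after allocation and only in one arm. A model with both arm and attendance no longer estimates the effect of being randomised to the programme. Depending on how controls are coded, the programme's effect can pass wholly into the attendance term. Section 4 of the SAP says that all analyses will strictly follow the plan, so an undefined statement of this kind can be read as a commitment. An analyst who carried it out in the most obvious way would get an arm estimate with no useful meaning. An analyst who followed section 26.b or the printed code would get a different one. The reader cannot tell from the text which is planned.

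The per-protocol comparison has a related weakness. It removes students from the intervention arm by their behaviour or their school's delivery, and removes nobody comparable from the control arm.

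**Working it through.** **Adherence figures (SAP Table 2, 15 intervention schools).** Summing the rows gives 709 high-risk students, 613 with at least one session and 561 with both.

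- At least one: 613/709 = 86.5%. Both: 561/709 = 79.1%. These agree with the printed 86% and 79%.
- The unweighted mean of the 15 school percentages for at least one session is 87.5%. The 88% in 18.d fits this mean, not a share of students.
- Five schools (1, 5, 9, 10, 12) fall below 85% on at least one session; seven (also 4 and 14) do so on both.
- Not both sessions: 709 − 561 = 148, or 20.9%. Exactly one session: 613 − 561 = 52.

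**Planned effect (SAP section 10).** Control risk 10%, intervention risk 5%. mITT OR = (0.05/0.95)/(0.10/0.90) = 0.474.

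**Assumptions.** The documents give no outcome risk by attendance. Let r be the untreated risk of non-attenders divided by that of attenders, varied from 0.5 to 2. Let q = 561/709 = 0.7913, with the effect acting only in students who attended both sessions. For an overall untreated risk of 10%:

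- attender untreated risk x = 0.10/(q + (1 − q)r)
- non-attender risk = r·x
- attender risk under the programme = x − 0.05/q = x − 0.0632

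**Attendance in the model, controls coded 0.** Arm and attendance then define three cells, so the arm OR is odds(r·x)/odds(0.10). At r = 2, x = 0.10/1.2087 = 0.0827 and r·x = 0.1655, so OR = 0.1983/0.1111 = 1.78. The attenders' risk does not enter, so the result is the same whether or not the programme works.

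**Per-protocol, all controls kept.** With no true effect, OR = odds(x)/odds(0.10). With the planned effect, OR = odds(x − 0.0632)/odds(0.10). The true OR in attenders is odds(x − 0.0632)/odds(x).

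| r | x | r·x | Arm OR, attendance-adjusted | Per-protocol OR, no effect | Per-protocol OR, planned effect | True attender OR |
|---|---|---|---|---|---|---|
| 0.5 | 0.1117 | 0.0558 | 0.53 | 1.13 | 0.46 | 0.41 |
| 1 | 0.1000 | 0.1000 | 1.00 | 1.00 | 0.34 | 0.34 |
| 1.5 | 0.0905 | 0.1358 | 1.41 | 0.90 | 0.25 | 0.28 |
| 2 | 0.0827 | 0.1655 | 1.78 | 0.81 | 0.18 | 0.22 |

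**Simulation check.** 200 runs per scenario, 15 + 15 schools of the Table 2 sizes (the same sizes assumed for controls), between-school coefficient of variation 0.35 as in section 10, logistic regression with cluster-robust standard errors. Median arm ORs for r = 0.5 / 1 / 1.5 / 2:

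- mITT, true effect: 0.48 / 0.48 / 0.50 / 0.48
- attendance-adjusted, controls 0, true effect: 0.55 / 1.02 / 1.40 / 1.79
- attendance-adjusted, controls 0, no effect: 0.50 / 0.95 / 1.41 / 1.76
- school percentage, controls 0, true effect: 0.50 / 1.47 / 2.52 / 4.50 (imprecise)
- school percentage centred at the intervention-arm mean, true effect: 0.47 / 0.47 / 0.45 / 0.41

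The second and third rows nearly coincide: with this coding the arm term measures selection, not the programme. The last row stays close to mITT, so the harm depends on a coding that the SAP does not give.

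**The case against.** The strongest reply is that no section specifying a model includes adherence. The statement stands only in two lists of deviations, and the adjustment list, the mITT definition and the printed code all leave it out. A reader might infer that the planned primary result is biased, or even reversed to show harm. The documents do not support that. Adherence could mean student attendance, the school percentage or the facilitator fidelity scores of section 18.b. A school percentage centred within the intervention arm barely moves the estimate. An arm OR above 1 also needs non-attenders at higher untreated risk than attenders, and the documents give no such figure. This part of the reply stands, and it narrows the point to an undefined statement that conflicts with the rest of the plan.

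It does not make the statement harmless. An OR of 0.53 at r = 0.5 looks like a preserved effect, but the same value arises when the programme does nothing.

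On per-protocol, it is fair that this is one sensitivity analysis beside mITT and of a familiar kind. A reader might infer that it must exaggerate benefit. It need not: with no true effect the bias is nil at r = 1 and runs against the programme at r = 0.5. Section 19 taken literally would also exclude every control, since none attended; that is hardly intended, but the text should say so.

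A complier-average analysis has limits too. It assumes that assignment does nothing for non-attenders, while protocol 1.6 and SAP 29 cite population-level benefits across the school grade. Defining exposure as both sessions further treats the 52 one-session students as unaffected. It is therefore better added with its assumptions stated than required as a replacement.

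**Conclusion.** The point holds as a defect of specification. The SAP twice commits to controlling for a post-randomisation quantity that control schools cannot have, without defining it, and contradicts its own adjustment list and printed code. Carried out with student attendance and controls at 0, it would give an arm OR between 0.53 and 1.78 for r from 0.5 to 2, unrelated to the programme's effect in attenders, in place of the planned 0.47. The printed primary code is not affected.

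The per-protocol comparison drops 20.9% of one arm and is not protected by randomisation. With no true effect its OR would lie between 1.13 and 0.81 over the same range, so the direction of bias is unknown.

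The Table 2 counts and planned rates are the documents' own. The range of r, and an effect confined to students with both sessions, are assumptions.

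**What to change.** 1. Delete the adherence-control statement from 18.d, item 4, and from item 5 of the closing deviation list. State in section 26 that the primary mITT model contains no covariate measured after randomisation. Report school-level adherence descriptively, as Table 2 already does.
2. In sections 18.c, 19 and 26.c, say that all high-risk controls are kept in the per-protocol analysis, and label it a non-randomised comparison.
3. Preferably add a complier-average causal effect with allocation as instrument and standard errors that respect school clustering. Use at least one session as the main exposure. In its simplest form it is the 48-month mITT risk difference divided by 0.86; the planned 5 points would become 0.05/0.8646 = 5.8 points (0.05/0.7913 = 6.3 with both sessions). State the assumption that assignment has no effect on non-attenders, and that grade-wide benefits could violate it.
4. Reconcile 88% in 18.d with 86% in Table 2 and the closing section, and say whether the figure is a share of students or a mean of school percentages.

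The cost is a few sentences and one further analysis on attendance data already held. That analysis will be less precise than mITT.
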